#### Co-primary endpoints

Two co-primary endpoints are defined: (1) an intervention adherence endpoint reflecting feasibility under real-world working conditions, and (2) an effectiveness-related endpoint assessing changes in musculoskeletal complaints. As this is a feasibility-oriented trial, effectiveness outcomes will be analyzed using an estimation-focused approach to quantify effect sizes and variability rather than to provide confirmatory hypothesis testing.

##### Co-primary intervention adherence endpoint

Intervention adherence will be evaluated based on predefined compliance and retention criteria. Task-level compliance will be quantified as the proportion of lifting-task time during which the exoskeleton is worn, with a target threshold of ≥ 50%. In addition, overall wearing time in relation to daily physical activity will be assessed using an objective proxy measure derived from smartwatch-based movement recordings attached to the exoskeleton (Garmin Vivoactive 4).

Study-level adherence (retention) will be assessed as the proportion of participants who remain in the study and provide outcome data through the final 3-month assessment, with a target retention rate of ≥ 75% (i.e., dropout ≤ 25%). While dropout of up to 50% is conservatively anticipated for planning purposes, retention ≥ 75% represents the desired feasibility target.

##### Co-primary effectiveness-related endpoint

The co-primary effectiveness-related endpoint is the change in musculoskeletal complaints from baseline to 3 months, assessed using the Cornell Musculoskeletal Discomfort Questionnaire (CMDQ) score, comparing the intervention group with the control group.

This endpoint will be analyzed using longitudinal models to estimate mean changes, effect sizes, and 95% confidence intervals. Given the feasibility focus of the trial, these analyses are intended to generate preliminary evidence and inform the design and sample size calculation of future adequately powered confirmatory studies. No formal multiplicity adjustment will be applied, as the trial is not powered for confirmatory testing.

##### Cornell Musculoskeletal Discomfort Questionnaire, German version (D-CMDQ) [31]

The “Cornell Musculoskeletal Discomfort Questionnaire” was developed in 1999 by Hedge et al. [38] and, in 2016, adapted by Kreuzfeld et al. [31] as a German-language version and validated (D-CMDQ). The questionnaire measures the subjectively perceived frequency and intensity of musculoskeletal pain and complaints, along with work-related impairments, for 20 body regions. It is economical, applicable to many occupations, and can be tested as individual or group.

Reliability: Internal consistency was assessed using Cronbach’s alpha for the frequency, severity, and work disorder subscales. This resulted in acceptable internal consistencies of α_frequency_ = 0.75, α_severity_ = 0.77 and α_work disorder_ = 0.82 [31].

Validity: To test convergent validity, the correlation between the D-CMDQ and the Numeric Rating Scale (NRS) was determined. According to Spearman, this resulted in medium to highly positive correlation coefficients [31].

Minimally clinically important difference/minimal detectable change: no information available.

#### Secondary outcome measurements and endpoints

##### National Aeronautics and Space Administration - Raw Task Load Index, German version (NASA-RTLX) [32]

The German version of the “NASA-RTLX” is based on the English-language long version by Hart & Staveland [39]. The questionnaire measures subjective workload on the subscales of mental, physical, and time demands as well as subjectively perceived performance, effort, and frustration. In the shortened version of the Raw-TLX questionnaire, the second part, which involves individual weighting of the subscales, is omitted.

Reliability: A Cronbach’s alpha of *α* = 0.84 indicates that the overall workload scale is highly reliable [40].

Validity: Positive results were observed regarding convergent, discriminant, and factorial validity [40].

Minimally clinically important difference/minimal detectable change: 15.8 to 24.3 points [41]

##### Fatigue Scale (FS) [33]

The “Fatigue Scale” is a German adaptation of the English version developed by Trudie Chalder and Simon Wessely [42]. It records fatigue levels and differentiates among three subscales based on the severity of physical and mental fatigue symptoms.

Reliability: High internal consistency was assessed for all scales: Cronbach´s alpha: α_total severity_ = 0.93, α_physical fatigue_ = 0.92, and α_mental fatigue_ = 0.86 [33].

Validity: Positive results were observed regarding convergent, discriminant, and factorial validity [33].

Minimally clinically important difference/minimal detectable change: no information available.

##### Copenhagen Psychosocial Questionnaire, German version (COPSOQ) [34]

The “Copenhagen Psychosocial Questionnaire” was originally developed by a Danish research team [43] and adapted by the Freiburg Research Centre for Occupational Sciences GmbH (FFAW) as a German-language version [34]. It was developed to measure psychosocial stress in an occupational context across all occupations and sectors. It also functions as a screening procedure for assessing psychological hazards in the workplace and, therefore, fulfills the test statistical quality criteria required by DIN EN ISO 10075-3. The German version is “available to all companies free of charge.” [34].

Reliability: Cronbach’s alpha for each subscale indicated good reliability (*α* = 0.68 to *α* = 0.89) [34].

Validity: Positive results were observed regarding convergent, discriminant, and factorial validity [34].

Minimally clinical important difference/minimal detectable change: 0.8 to 5.9 points [44]

##### Vienna Test System for cognitive performance diagnostics (WTS) [35]

The Vienna Test System (WTS) is an advanced software solution designed for psychological performance diagnostics. It is a widely used instrument that has proven to be reliable and valid in various studies. The WTS is used in areas such as neuropsychological diagnostics, aptitude diagnostics, and research [35].

Three tests for cognitive performance diagnostics are used in the ELSA LogiCare trial. The *SPAN method* measures verbal working memory and enables differentiated categorization of test subjects across a broad performance spectrum [45]. The *TACO* assesses selective attention, long-term concentration maintenance, and divided attention skills. [46]. The *Trail Making Test* (TMT) measures the speed of visuomotor processing and cognitive flexibility [47].

Minimally clinically important difference/minimal detectable change: no information available.

##### Short Scale Technology Commitment (TB) [36]

The “Short Scale Technology Commitment” aims to predict the effective use of new technologies. It subjectively measures three key determinants: technology acceptance, technology competence, and technology control beliefs. The scale, which consists of 12 items, is cost-effective and not restricted to any particular technology.

Reliability: With a Cronbach’s alpha of α = 0.84 in each case, the overall scale, the technology acceptance subscale, and the technology competence subscale demonstrated high reliability. An acceptable internal consistency of *α* = 0.74 was determined for the technology control subscale [36].

Validity: Three validation studies observed positive results regarding convergent, discriminant, and incremental validity [36].

Minimally clinically important difference/minimal detectable change: no information available.

Quebec User Evaluation of Satisfaction with Assistive Technology 2.0 (QUEST 2.0) [37]

The German version of the “Quebec User Evaluation of Satisfaction with Assistive Technology 2.0” is based on the English version of the same name by Demers et al. [37]. The questionnaire assesses satisfaction with an assistive device through two subscales: satisfaction with the device itself and satisfaction with the related service.

Reliability: For internal consistency, acceptable values of Cronbach’s alpha *α* > 0.7 were determined [48].

Validity: Positive results were observed regarding convergent, discriminant, and factorial validity [37].

Minimally clinically important difference/minimal detectable change: no information available.

### Participant timeline {13}

Trained research staff members will provide detailed explanations about the study objectives, processes, harms, and participants’ rights. They will respond to any questions from participants or representatives and ensure a complete understanding of the information provided. Once participants have successfully enrolled in the study, they will be randomly assigned to either the control or intervention group, followed by a baseline assessment.

The study visits for data collection are identical in both groups. During the intervention period, four assessments will be conducted: a baseline assessment with medical history collection, instructions, and training on the correct use of the exoskeleton; two follow-up assessments with questionnaires and short interviews administered at 4-week intervals; and a final assessment conducted 3 months later (Fig. 1).

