### Recruitment {15}

We assume that cooperation agreements will have to be concluded with several companies and hospitals to achieve the planned number of cases. It is planned to conduct three survey waves, each lasting 6 months (3 months of intervention followed by 3 months of exchange in the waiting-control design). As a result, a recruitment period totalling 18 months is planned.

Before the cooperation agreements are finalized, site visits will be conducted at the companies and hospitals. During the first contact between employees of the participating companies and the trial staff, information will be provided regarding the purpose and procedures of the trial. At this stage, employees will receive written information as well as detailed informed consent. After an appropriate period for consideration, participants will have the opportunity to ask questions, verification of inclusion and exclusion criteria will be conducted, and written consent will be obtained. Following this, participants will be enrolled in the trial, and the scheduling of the baseline assessment will occur.

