### Concealment mechanism {16b}

Allocation concealment will be ensured through centralized computer-based randomization. Group assignment is generated by the randomization software only after a participant has been enrolled and baseline eligibility has been confirmed. Investigators involved in recruitment and enrollment will not have access to the upcoming allocation sequence.

Due to the visible and physical nature of the intervention (use of a back-support exoskeleton), blinding of participants and intervention personnel is not feasible.

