## Data collection and management

### Plans for assessment and collection of outcomes {18a}

No formal pre-screening data are collected prior to enrollment. Recruitment is based on voluntary participation within cooperating companies. Interested employees receive detailed study information and are enrolled after providing written informed consent, provided that inclusion criteria are met.

Baseline data collection is initiated after enrollment. Outcome assessments will be conducted on-site at the participating companies and hospitals. Data collection includes sociodemographic characteristics and a brief personal medical history obtained through an open-ended questionnaire administered at baseline.

Outcome parameters are documented in standardized data sheets and entered into a secure database. Table 3 provides a detailed schedule of participation and measurement time points, including the constructs to be assessed and the corresponding validated instruments. All assessments will be conducted and monitored by trained study personnel at predefined time points to ensure the quality, consistency, and comparability of the collected data.

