### Plans to promote participant retention and complete follow-up {18b}

No changes are planned for the assigned intervention, as the study aims to evaluate the practical usability of the exoskeleton under real-world working conditions. If participants discontinue the intervention (e.g., due to discomfort), these decisions will be considered meaningful outcomes that provide valuable insights into user acceptance.

To encourage participant engagement and promote data completeness, questionnaires are administered using the online survey platform LimeSurvey [49]. For each assessment, participants receive an email invitation containing a personalized survey link. Participants have a 1-week period to complete each questionnaire. If a questionnaire has not been completed within 5 days, an automated reminder email is sent. Within the questionnaire, most items are mandatory and participants cannot proceed without providing a response, thereby minimizing item-level missing data.

Any study dropouts and instances of non-response at the questionnaire level will be documented. All collected data will be included in the analyses in accordance with the statistical methods described below.

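### Randomisation is placed before the baseline assessment in an open-label waitlist trial, so the self-reported baseline D-CMDQ behind the change-from-baseline co-primary may be given with the arm already known

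*Protocol article*

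**What the plan says.** Participant timeline {13} gives the order directly: after enrolment, "they will be randomly assigned to either the control or intervention group, followed by a baseline assessment". The same section describes that first visit as "a baseline assessment with medical history collection, instructions, and training on the correct use of the exoskeleton".

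The other sections do not reverse this order:

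- Concealment mechanism {16b}: "Group assignment is generated by the randomization software only after a participant has been enrolled and baseline eligibility has been confirmed". The condition is eligibility, not completed outcome data.
- Recruitment {15}: after consent, "participants will be enrolled in the trial, and the scheduling of the baseline assessment will occur".
- Plans for assessment and collection of outcomes {18a}: "Baseline data collection is initiated after enrollment". It does not say whether this comes before or after randomisation.
- Table 3 puts randomisation, exoskeleton training and the D-CMDQ in the same t0 column, with no order within the visit. The D-CMDQ appears again only at t3.

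The effectiveness co-primary is "the change in musculoskeletal complaints from baseline to 3 months", compared between the intervention and control groups. The D-CMDQ section describes the instrument as a subjective self-report. Who will be blinded {17a} states that participants are not blinded, and Trial design {8} states that controls receive the device after the intervention phase.

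**The concern.** A baseline value should be fixed before anyone can react to the allocation. Here the stated sequence makes it a post-randomisation measurement, given by people who may know whether they have a device or are waiting for one. Someone about to receive a device may rate present complaints differently from someone told to wait. Such a difference does not come from treatment, yet it enters a change score as if it did.

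The safeguards in {17a} do not reach this. The participant is the rater of the D-CMDQ, so blinded outcome assessors and analysts do not help, and concealment protects the assignment rather than later answers. That section concedes performance and detection bias in subjective outcomes generally, but does not mention a baseline reported after allocation.

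At stake is the effect estimate, which Sample size {14} says will inform the design and size of later confirmatory trials. The other baseline self-reports (NASA-RTLX, Fatigue Scale, COPSOQ, technology commitment, sick days) share the exposure.

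**Working it through.** **No stated figure to reproduce.** The point concerns the order of steps, and the sections quoted above settle that order. The arithmetic below only shows what a baseline reporting shift would do.

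**Inputs from the protocol article.** 80 intervention and 40 control complete datasets (Sample size {14}); D-CMDQ at t0 and t3 only (Table 3); a mixed model in which the values from all visits are the dependent variable, with group, categorical time, their interaction and a random intercept ({20a}).

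**Assumptions not in the documents.** No true effect; a uniform reporting shift b at baseline in the intervention arm, in SDs of the D-CMDQ score, absent at month 3; equal variance at both times; correlation rho between baseline and month 3.

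**Step 1, bias by contrast.**
- Change (group-by-time) contrast: (month-3 difference) − (baseline difference) = 0 − b = −b. The shift passes through in full.
- Month-3 between-group contrast: 0. The baseline shift does not enter.

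A simulation of the random-intercept REML model (200 runs, complete data, 80 versus 40, b = 0.2, rho = 0.6) agrees. The change contrast averaged −0.18 (Monte Carlo SE 0.01) against −0.20 expected, and the month-3 contrast averaged 0.02 (SE 0.01).

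**Step 2, size relative to precision.** Half-width of the 95% CI for the difference in change:

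1.96 × sqrt(2(1 − rho)) × sqrt(1/80 + 1/40), with sqrt(1/80 + 1/40) = sqrt(0.0375) = 0.194.

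| rho | sqrt(2(1 − rho)) | SE | half-width | 0.2 / half-width |
|---|---|---|---|---|
| 0.3 | 1.183 | 0.229 | 0.449 | 45% |
| 0.5 | 1.000 | 0.194 | 0.380 | 53% |
| 0.7 | 0.775 | 0.150 | 0.294 | 68% |

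**Step 3, how often the interval would mislead.** Under the same assumptions and no true effect, the 95% CI for change excludes zero in 8% to 10% of trials at b = 0.1 and 18% to 27% at b = 0.2 (rho 0.5 to 0.7), against a nominal 5%. More participants do not reduce b; they narrow the interval around the biased value.

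**Step 4, do the planned analyses catch it?** The complete-pair sensitivity analysis in {20a} uses within-group paired t-tests, which subtract the same baseline, so it offers no check.

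**The case against.** **The timing could be read too strongly.** {18b} says questionnaires are e-mailed as links and "Participants have a 1-week period to complete each questionnaire". A reader might infer that exoskeleton participants answer the baseline up to a week after training and first use. The documents do not support that as fact: {18a} says outcome assessments take place on-site, run by trained staff at predefined time points. They do not say whether the baseline questionnaire is completed at the visit or afterwards, when device use begins relative to it, or when the participant is told the arm. What stands is that randomisation is placed first and nothing requires the questionnaire before the arm is known.

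**The bias may not reach the reported estimate.** {20a} promises group contrasts for the 3-month period, which could mean the month-3 difference. On that reading the shift drops out. This stands as a limit on the point, but the endpoint itself is defined as change, and that contrast carries the shift in full.

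**The size and direction are unknown.** This stands. Controls might over-report or under-report, and a reporting shift that lasted to month 3 would cancel in the change score.

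**The endpoint is not confirmatory.** This also stands. Effectiveness is estimated without a powered test, the adherence co-primary does not use the baseline D-CMDQ, and the month-3 D-CMDQ is unblinded self-report whatever the order. It lowers the urgency but does not excuse an avoidable bias in an estimate meant for planning later trials.

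**Conclusion.** The point holds in a limited form. The stated order puts randomisation before baseline, and allocation is released "only after a participant has been enrolled and baseline eligibility has been confirmed", so the baseline D-CMDQ may be reported with knowledge of the arm. A differential shift of b SD would bias the change contrast by b and leave a pure month-3 contrast unaffected.

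The 45% to 68% range rests on assumed values (b = 0.2 SD, rho 0.3 to 0.7, 80 versus 40 completers) and is an illustration, not an estimate. A reader might go further and conclude that the effect estimate is biased, or that the trial is invalid. Neither follows: the documents do not state when the arm is disclosed, give nothing on the size or sign of b, and leave the contrast open. This should be fixed, but is not a fatal fault.

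**What to change.** 1. Require completion of the baseline self-report questionnaires (D-CMDQ, NASA-RTLX, Fatigue Scale, COPSOQ, technology commitment, sick days) before the randomisation software releases an allocation, either at the baseline visit or by link beforehand.
2. Align {13}, {16b}, {18a} and Table 3 to one order: consent, baseline questionnaires, randomisation, training. The heart-rate and blood-pressure readings, taken over 3 days, need not hold up allocation. If practice already follows this order, {13} misdescribes it and only the text needs correcting.
3. Recruitment began in January 2026. For participants already enrolled, record the dates of baseline completion and allocation. Then run a sensitivity analysis that excludes baselines given after allocation, or that uses the month-3 between-group contrast. In the first option, drop the baseline value and not the participant, so that the randomised groups stay intact.

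Cost: a short amendment, and possibly a brief delay to allocation and training when a questionnaire is not finished at or before the visit. No additional participants are needed.

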**Fig. 1 Fig1:**
[figure not shown]
Flow chart. The trial is conducted using a waiting-control design. The control group receives the exoskeletons after the intervention period for 3 months. The wearing time of the control group is not shown in the flow chart as it is not included in the analysis

### Sample size {14}

This study is designed as a feasibility-oriented randomized controlled trial with a primary focus on intervention adherence under real-world working conditions. Primary feasibility outcomes include the following: (1) *task-level compliance with exoskeleton use* (worn for at least 50% of the time during lifting tasks) and (2)* study-level adherence* (defined as at least 75% retention through the 3-month assessment). The sample size is therefore primarily determined by feasibility considerations, including the availability of exoskeleton devices, recruitment capacity within cooperating companies, and the fixed project timeline.

Due to the lack of comparable prospective long-term studies on passive back-support exoskeletons in occupational settings, a formal a priori sample size calculation based on expected effect sizes for musculoskeletal outcomes was not feasible. Consequently, the study is not powered to provide confirmatory evidence regarding effectiveness-related outcomes.

Participants will be randomized using a 2:1 allocation ratio (intervention to control). The recruitment target is defined in terms of evaluable participants: 80 complete datasets in the intervention group and 40 complete datasets in the control group (total *n* = 120 complete datasets). A complete dataset is defined as outcome data available at baseline, at two intermediate follow-up assessments after 1 and 2 months, and at the final assessment after 3 months.

Given the real-world occupational setting and the multi-visit follow-up schedule, substantial attrition is anticipated. Assuming a conservative dropout rate of up to 50%, achieving 120 complete datasets may require randomizing up to approximately *N* = 240 participants (≈160 intervention, ≈80 control). Recruitment will therefore continue until these complete-dataset targets are reached, or until a maximum of *N* = 240 participants have been randomized, whichever occurs first, subject to feasibility constraints (e.g., device availability, company participation, and project timeline). The recruitment stopping rule is based on follow-up completeness and feasibility considerations and is not linked to interim effectiveness results.

Effectiveness-related outcomes will be analyzed using longitudinal models to estimate effect sizes, variability, and 95% confidence intervals rather than to formally test hypotheses. These estimates, together with feasibility parameters, will be used to inform the design and sample size calculation of future adequately powered confirmatory trials.

